**Fig. 2 Fig2:**
[figure not shown]
Participant screening procedure

### Aim

This is a pilot study designed to answer the following primary research questions:i.Is the ‘Get Healthy!’ program feasible to implement in participants with mild-moderate ID, aged 40 years and over, and their carers?ii.Are the instruments and procedures being used to collect clinical outcome measurement data feasible to administer to participants with mild-moderate ID, aged 40 years and over?

The secondary aim of the study is to determine, in a small sample, if any pre-post program changes occur across the following clinical outcome measures: body mass index, waist circumference, cardiovascular fitness, physical activity (amount and intensity) and sedentary behaviours, resting blood pressure, functional strength/capacity, dietary intake (energy intake, food group consumption and diet quality), dietary and physical activity knowledge, and quality of life.

## Methods

### Design

This is a single intervention pilot feasibility study.

### Study population

Inclusion/exclusion criteria: Participants with mild to moderate intellectual disability and their carers will be recruited into the study. Level of ID will be determined based on the report of referring disability agencies or primary caregivers. In order to test the feasibility of the ‘Get Healthy!’ program for older adults with ID, participants aged 40 years and over will be preferentially recruited. Participants deemed to be at extreme psychiatric, behavioural or physical health risk, and participants with an insufficient range of motion to participate in the physical activity component of the program will be excluded from the study. Full inclusion and exclusion criteria for both the person with ID and carer groups are outlined in Fig. 2.

Sample size: As this is primarily a feasibility study, it is not powered to demonstrate statistical significance. Between 8 and 10 adults with intellectual disability and carers in total will be recruited using convenience sampling. This sample size and recruitment methodology is based on the research teams’ previous recruiting experience with this difficult to access population. Limiting the study sample size will also allow us to engage with each participant’s progress in a detailed fashion. We will seek comprehensive feedback from each individual in order to refine the program for future use.

Recruitment and screening: Participants will be recruited from a defined target area in metropolitan NSW, Australia. Intellectual disability service and housing providers, partner organisations and peak bodies within the target area will be approached to advertise the study. Potential participants meeting inclusion criteria will undertake a multi-stage screening procedure prior to enrolment. The screening pathway is outlined in detail in Fig. 2 and includes the following:I.Obtaining informed consent from the person or proxy consent from their next of kin or guardian as required by law. Capacity to provide consent will be based on a combination of carer/disability service provider feedback and research team assessment.II.Completion of the Exercise and Sports Science Australia (ESSA) adult pre-exercise screening tool [43] (carer participants—protocol A). Participants with ID also to complete, with some modifications including tool to be completed in conjunction with qualified exercise physiologist and carer where relevant, language in tool has been simplified to increase accessibility, addition of a screening question for people with Down’s syndrome related to spinal cord compression or atlantoaxial instability, and all participants with ID to be referred for medical clearance irrespective of screening tool results.III.Obtaining medical clearance to participate (all participants with ID, as well as all carer program A participants with a positive score on stage 1 of the ESSA screening tool). The research team will offer to reimburse costs relating to attending the medical clearance appointment.

If we have a greater number of people applying for the trial than we have spaces available, we will consider factors such as gender (with the aim of ensuring both men and women are represented in the sample) and age (preferentially recruiting participants who fall into our target range of 40 years and over).

### Data collection timeline

Table 2 summarises the data collection timeline for all outcome measures.

**Table 2 Tab2:** Outcome measures and data collection points

Outcome measure		Time point (weeks)													
		0 Baseline	1	2	3	4	5	6	7	8	9	10	11	12	13 Completion
Attendance and participation		X	X	X	X	X	X	X	X	X	X	X	X	X	X
Body mass index	Height	X													
	Weight	X						X							X
Waist circumference		X						X							X
Blood pressure		X						X							X
Cardiovascular fitness YMCA sub-maximal ergometre test − 12-min duration	minutes/stages performed	X						X							X
	Peak HR (%APMHR)	X						X							X
	Peak workload achieved	X						X							X
Physical activity level and sedentary behaviour	Self/proxy report	X													X
	Actigraph data	X													X
Physical strength tests	30-s modified push up test	X													X
	Medicine ball throw/chest pass	X													X
	10RM testing	X													X
	30-s sit to stand test	X													X
Quality of life		X													X
Dietary intake assessment	3-day photographic food record	X													X
	Proxy-assisted 24-h recall	X													X
Nutrition and physical activity knowledge		X													X

### Outcome measures

The feasibility indicators described below are the primary outcome measures being assessed in this pilot. Clinical outcomes will be explored as secondary outcome measures.

### Feasibility outcomes

Participation rates: Individual participation in each week’s nutrition session and each physical activity sessions will be scored:0 = Did not attend1 = Attended but only participated minimally. For example, attempted < 50% of activities, did not join in group discussions2 = Attended and participated moderately well to very well. For example, engaged in > 50% of activities, was part of group discussions.

At the completion of the intervention these scores will be totalled and participants will be categorised into high (100–75% score), medium (50–74% score) or low (< 50% score) participation groups for the purposes of analysis.

Drop-out rates and reasons: Drop-out rates and reasons will be recorded to help determine the acceptability of the program to participants.

Acceptability of data collection measures and procedures: The distribution of missing data within each measure will help to determine the acceptability of measures to program participants. Exit interviews will also be conducted with all participants to capture qualitative data on the acceptability of the program and data collection measures for individual participants. Exit interview schedules have been designed with accessible language to enable participation. All interviewers will have had previous experience leading interviews or focus groups with people with ID.

Adverse outcomes: Participants who develop any physical injury or other emerging health issue during the trial will be referred back to their GP for review and clearance prior to continuing. Participants displaying psychological distress will be referred to relevant mental health support services. All adverse physical and psychological outcomes will be recorded and reported in subsequent publications.

Benchmark results indicating a definitive larger scale trial may be feasible will include the following:Drop-out rate of < 70%A majority of participants (> 60%) achieving ‘high’ or ‘medium’ participation scoresPositive qualitative feedback from > 80% of participants regarding their experience of undertaking the programThe feasibility of each individual outcome measure will be assessed separately. If less than half of participants were able to complete the outcome measure the research team will review in detail reasons for failure to implement the measure. Based on this review, we will either modify how the measure is implemented in the larger trial (for example, providing participants with additional prompts and support to complete a measure), or replace the outcome measure if it appears impractical to implement in our target population.

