Many barriers exist for people with ID who seek to access healthy lifestyle programs to address these risks. These include lack of transport; lack of funding; stigma, a workforce that is insufficiently equipped to tailor interventions to the unique needs of this population; cognitive, behavioural and communication challenges; and a lack of universal design in urban planning that prevents some people with co-morbidities from accessing public exercise areas [1, 25, 26]. Compared to the robust knowledge base detailing healthy lifestyle interventions in the general population, i.e. [27], less is known about the efficacy of lifestyle interventions for people with ID [28]. Recruitment challenges and the additional complexities of obtaining ethics approvals to include people with ID in clinical trials [29, 30] mean that this population has been underrepresented in healthy lifestyle trials to date. Information about how outcome measures can best be tracked across trials are also lacking as many measurement tools have not been validated in this population.

The small number of ID specific physical activity and healthy eating intervention trials reported in the literature to date has resulted in improvements in fitness and psychosocial functioning [31]. Potential for weight loss appears most likely when both physical activity and nutrition needs are addressed simultaneously [32] within a comprehensive health behaviour education program [31]. Making interventions person centred, facilitating carer involvement [10], providing a higher frequency of session and level of support and sufficiently tailored content, design and delivery also appear to improve effectiveness [33]. For example, Melville and colleagues’ [34] intervention that used a combination of behavioural change techniques, carer involvement and physical activity and nutrition-related supports, produced significant decreases in weight, waist circumference and sedentary behaviours for participants with ID.

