**Fig. 1 Fig1:**
[figure not shown]
Development of the ‘Get Healthy!’ program. The project steering committee members invited to provide feedback were [name], [name], [name], [name], [name], [name], [name], [name], [name], Assoc. [name], [name], [name] and [name]. Additionally, nutrition and exercise physiology student researchers [name], [name], [name], [name], [name], [name], [name] and [name] contributed to the program design

A summary of physical activity and nutrition content, and session structure, as well as required equipment, is provided in Table 1. Participants in the ‘Get Healthy!’ program engage in a minimum of three contact hours each week, for a continuous 12-week period. Contact hours are made up of two 1-h physical activity sessions, held on non-consecutive days, and 1 h per week of guided nutrition information and support. In order to decrease participant time and transportation burden, we will run the weekly nutrition session immediately before or after one of the exercise sessions. Participants will therefore only need to attend the program on two out of 7 days per week. The physical activity component of the program is delivered by an accredited exercise physiologist, and the nutrition-related component of the program is delivered by an Accredited Practicing Dietitian. Both of these program leaders have previous experience running interventions for people with intellectual disability. Intervention intensity and advice is tailored to the individual needs of each participant; however, the program is ideally delivered in a small group setting (three to six people per group). The program can be run in a number of settings; however, access to specialised exercise and monitoring equipment is required for pre- and post-testing as well as some of the physical activity sessions*.* In order to support sustained behaviour change post-intervention, the exercise physiologist will also provide examples throughout the program of accessible and low-cost ways to increase physical activity without specialised equipment.

**Table 1 Tab1:** ‘Get healthy!’ curriculum content

Component	Time commitment	Topics	Resources required^a^

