Nutrition	12-week program consisting of the following: One face-to-face 60 min session per week Plus additional follow-up phone calls/prompts during food intake monitoring periods. Phone calls will be made either directly to the participant or to their carer depending on the person’s level of independence.	The style of presentation will be tailored to the abilities of participants. The nutrition *education* component will be presented to all participants and will cover the following topics: • The five food groups • Discretionary foods and healthy snacks • Healthy drinks • Portion size and mindful eating • Eating out choices • Shopping/eating out tour	Equipment: • Scale • Stadiometre • Cameras for each participant • 24-h proxy food recall form • Folder for each participant to keep their handouts • White board • Computer and projector Handouts: • Instructions to complete 3-day digital photography food record • 12-week challenge checklist • ID-adapted Australian dietary guidelines • Nutritional goals and barriers • Weight and BMI • Information about discretionary foods, fruits and vegetables. • Information about the grain, meat and dairy food groups • Healthy snack choices • Are you drinking enough water? • Drink ideas • Healthy plate model, hunger scale and mindful eating • Healthier eating/takeaway options • What to think about when eating out • Healthy Eating Graduate certificate

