Physical activity	12-week program consisting of the following: Two 60-min face-to face sessions per week on non-consecutive days. Breakdown of components within each session: - 10% didactic information - 40% aerobic exercise - 30% strength-based exercise - 20% balance-based exercise	The physical activity *education* component will cover the following topics: • What it means to be healthy • Consequences of obesity • Physical activity and screen time guidelines • Appropriate goal setting • Planning for maintenance and self-management • Barriers to Physical activity and how to address them The physical activity *practical* component will be comprised of a combination of aerobic and strength- and balance-based exercise. Types of exercises and exercise intensity to be tailored to abilities and interests of each participant but may include activities such as: cycling on a stationary bike, walking, supported row, horizontal squat, stair climbing, tandem, body weight exercises such as wall push-ups, light dumbbell work.	Equipment: - GTX3+ accelerometres for each participant - Blood pressure Sphygmomanometre and stethoscope - Scale - Stadiometre - Measuring tape - Stationary bikes (including a Monark resistance-based ergometre) - Heart rate monitors - Stop watch - Trundle wheel - Medicine balls - Parallel bars - Stairs - Boxing equipment - Chairs - Exercise mats - Cones - Dumbbells - Horizontal squat machine - Supported row machine - Rower Handouts: - ‘Goal setting’ - ‘Counting our steps’

^a^Handouts listed here are for participants with mild to moderate intellectual disability. They may be modified further depending on the needs of individual participants. Carers participating in Program A will be offered the same information in handouts tailored to their level of health literacy

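### The pooled participation score lets exercise stand in for nutrition, so the > 60% participation benchmark can be met with poor or absent nutrition-session participation

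*Protocol article*

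**What the plan says.** The Protocol article describes a program with two components. In the section on the background to the program, the weekly load is given as "Contact hours are made up of two 1-h physical activity sessions, held on non-consecutive days, and 1 h per week of guided nutrition" support, delivered "for a continuous 12-week period". Table 1 repeats the split: for nutrition, "One face-to-face 60 min session per week"; for physical activity, "Two 60-min face-to face sessions per week on non-consecutive days". An exercise physiologist leads one component and a dietitian the other.

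Under Feasibility outcomes, each nutrition session and each physical activity session is scored 0 (absent), 1 (present, minimal participation) or 2 (moderate to very good participation). The aggregation rule follows: "At the completion of the intervention these scores will be totalled and participants will be categorised into high (100–75% score), medium (50–74% score"), and low for anything under 50%. The resulting groups are intended for use in the analysis. No subtotal, weight or minimum by component is stated.

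The benchmarks for a larger trial then include "A majority of participants (> 60%) achieving" a 'high' or 'medium' score. The others concern drop-out, positive feedback on the program as a whole, and whether each outcome measure could be completed.

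**The concern.** Participation is one of the feasibility indicators that the article names as primary outcomes, and the first primary question asks whether the program can be implemented. That program is a combination by design. The Background supports this with the remark that "Potential for weight loss appears most likely when both physical activity and nutrition needs are addressed simultaneously", and dietary intake and knowledge are among the secondary outcomes.

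A single total over both kinds of session allows compensation: strong exercise participation can offset weak or absent nutrition participation. Exercise has twice as many sessions, so compensation works much better in that direction than in reverse. If it is large enough, the benchmark can be reported as met while the nutrition sessions were not feasible, and the program could go forward without that being flagged. The participation groups could also place people with very different exposure to the nutrition sessions in the same category.

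**Working it through.** **Inputs.** Two exercise sessions and one nutrition session per week for 12 weeks (background section and Table 1); 0 to 2 points per session, cut-offs at 50% and 75%, and the > 60% benchmark (Feasibility outcomes); 8 to 10 participants in total (Sample size). The article gives no maximum score, so there is no stated figure to reproduce.

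**Maximum score.**
- Exercise: 12 × 2 × 2 = 48
- Nutrition: 12 × 1 × 2 = 24
- Total: 48 + 24 = 72, of which exercise is 48/72 = 66.7% and nutrition 24/72 = 33.3%

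**Cut-offs in points.** 'Medium' starts at 0.50 × 72 = 36 and 'high' at 0.75 × 72 = 54.

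**Participation patterns under the pooled rule.**

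| Exercise | Nutrition | Pooled score | Category |
|---|---|---|---|
| 48 (full) | 0 (none attended) | 48/72 = 66.7% | medium |
| 36 (e.g. 18 of 24 sessions scored 2) | 0 | 36/72 = 50.0% | medium |
| below 36 | 0 | below 50% | low |
| 48 | 6 (3 of 12 sessions scored 2) | 54/72 = 75.0% | high |
| 48 | 12 (every session scored 1) | 60/72 = 83.3% | high |
| 0 | 24 (full) | 24/72 = 33.3% | low |

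So 'medium' without any nutrition session requires 36/48 = 75% of the exercise points. 'High' cannot be reached on exercise alone; it needs at least 54 − 48 = 6 nutrition points.

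**Benchmark.** The smallest counts above 60% are 5 of 8 (62.5%), 6 of 9 (66.7%) and 7 of 10 (70.0%). If that many participants each earn at least 36 exercise points, the benchmark is met whatever the nutrition scores are.

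**Sensitivity.** Table 2 marks attendance from week 0 to week 13. If 13 or 14 weeks were scored at the same two-to-one ratio, full exercise alone would still give 66.7%, because the number of weeks cancels.

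**Same scores by component.**
- Full exercise, no nutrition: exercise 48/48 = 100% (high), nutrition 0/24 = 0% (low).
- Full exercise, 3 nutrition sessions scored 2: nutrition 6/24 = 25% (low).
- Full exercise, every nutrition session scored 1: nutrition 12/24 = 50% (medium, exactly at the cut-off).

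Separate totals therefore expose non-attendance. Uniformly minimal nutrition participation moves from a pooled 'high' to a nutrition score of 'medium', which is more accurate but would still count towards the benchmark.

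**The case against.** The best defence is that the two-to-one weighting mirrors the planned contact hours. Giving each session equal weight yields the share of the face-to-face program that a person took up, which is a reasonable adherence measure, and the asymmetry follows from the dose split. This stands for the pooled score as a summary. It does not make that score able to test each component.

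Second, an unattended nutrition stream would hardly go unnoticed. Every session is scored, attendance is tracked weekly, there are at most 10 participants, all have exit interviews, and the findings are meant to refine the program. The benchmarks are also worded as signs that a larger trial may be feasible, not as an automatic rule. This stands, and it limits the consequence. The stated benchmark would still read as met, and nothing in the text calls for a component breakdown.

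Third, the article may condense a fuller plan. A tabulation by component could well sit there. But the scoring, the cut-offs and the benchmark are fixed in the article itself, and as written they are pooled.

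A reader might infer stronger claims, which the document does not support:
- *Anyone who skips nutrition still rates 'medium'.* Only with at least 36 of 48 exercise points; otherwise the rating is 'low'.
- *A zero nutrition score means that the dietary component was not received.* Table 1 also lists follow-up calls and prompts to the participant or carer during food-intake monitoring, which the score does not count.
- *Participants would skip the nutrition hour by arriving late or leaving early.* This is speculation. The hour is placed next to an exercise session to ease attendance, which makes selective absence less likely.
- *An unused nutrition arm would be carried forward.* There is no such arm in this single-intervention study, and the step from a met benchmark to that outcome is not established.

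**Conclusion.** The point holds as a limitation of the benchmark. With the stated rule, no nutrition attendance is compatible with 'medium' (50.0% to 66.7%, given 36 to 48 exercise points), and minimal participation in every nutrition session is compatible with 'high' (83.3%, given full exercise). The > 60% criterion can be met by 5 of 8, 6 of 9 or 7 of 10 such participants, and no other stated benchmark has a threshold for the nutrition sessions.

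This rests on reading the rule as one pooled total, which is its natural sense, and on counting the benchmark over all 8 to 10 people recruited. It shows what the score permits; it does not predict that participants will behave this way. The consequence is modest, but the change is worth making because participation is a primary outcome and the correction is nearly free.

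**What to change.** In the participation and benchmark paragraphs of Feasibility outcomes:

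1. Total and categorise the same 0 to 2 scores separately for exercise (out of 48) and nutrition (out of 24), with the existing cut-offs.
2. Report the share of participants at 'high' or 'medium' for each component against > 60%.
3. Keep the pooled total as a descriptive summary of contact-hour dose.
4. State that if a component falls short, its feasibility has not been shown and it will be reviewed before the larger trial.

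Because uniformly minimal nutrition participation falls exactly on the 50% cut-off, it also helps to show the distribution of 0, 1 and 2 scores by component.

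The cost is a few sentences. The scores are already recorded per session, so there are no new data and no added burden on participants. The small downside is that the participation benchmark becomes harder to meet in full.

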Data analysis plan: Quantitative data will be analysed using the Statistical Package for Social Science (SPSS). Given the small sample size, primary analysis will focus on descriptive statistics and confidence interval estimations for outcomes of interest. While this trial is not powered to detect statistically significant differences, we will use paired *t* tests in an exploratory fashion to analyse normally distributed continuous variable data collected at two timepoints only (baseline and 13 weeks). The nonparametric Wilcoxon signed-rank test will be used in cases where data are not normally distributed. To explore any group effects of the intervention when there are two timepoints, we will calculate the difference between completion and baseline timepoints for each measure and then compare the mean of the differences using *t* tests. Regression modelling adjusting for clustering will be used to analyse data collected at three or more timepoints. Appropriate imputative techniques will be used to account for any missing data points where appropriate. We will also analyse the impact of gender on feasibility and clinical outcomes. This analysis will be exploratory in nature in view of the small sample size. Qualitative data collected from exit interviews will be digitally recorded and transcribed verbatim. Transcribed data will be thematically analysed to identify program strengths, weaknesses, suggestions for improvement, and overall perceived impact. The software program NVivo (version 11.0.0) will be used to support organisation of qualitative data.

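### The participation total is replaced by high/medium/low groups as the analysis variable, although only the feasibility benchmark needs the groups

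*Protocol article*

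**What the plan says.** Participation is one of the feasibility indicators, which the protocol article names as its primary outcomes (Outcome measures). Under Feasibility outcomes, "Individual participation in each week’s nutrition session and each physical activity sessions will be scored" on a three-level scale: 0 for absence, 1 for minimal participation, and 2 for the top level, described as "Attended and participated moderately well to very well". The scores are totalled when the programme ends, and then "participants will be categorised into high (100–75% score), medium (50–74% score) or low (< 50% score) participation groups for the purposes of analysis".

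The same section uses the groups once more. One benchmark for going on to a larger trial is that more than 60% of participants are in the high or medium group.

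The data analysis plan (last paragraph under Clinical outcomes) says that "primary analysis will focus on descriptive statistics and confidence interval estimations for outcomes of interest". It adds: "We will also analyse the impact of gender on feasibility and clinical outcomes", and calls that analysis exploratory because the sample is small. The sample is 8 to 10 people in total, carers included, and the study is stated not to be powered for significance (Study population). Nowhere does the article say that the participation total is analysed or reported on its own scale.

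**The concern.** The benchmark is a yes/no rule and needs a cut. Estimation and group comparison do not. The wording makes the three groups the variable for analysis in general, so it reaches the planned estimates and, on its natural reading, the gender analysis of feasibility outcomes.

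Three things are at stake. Participants with quite different engagement become identical, while near neighbours on either side of a cut become different. With 8-10 people there is little information to spare. And the pilot is meant to refine a sufficiently powered trial, but three counts supply no mean or SD of participation for that purpose.

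**Working it through.** The plan has no calculation of its own on this point to reproduce, so the check builds up from the scoring rule.

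**1. Range of the score.** Inputs: the programme runs "for a continuous 12-week period", with "two 1-h physical activity sessions, held on non-consecutive days, and 1 h per week of guided nutrition information" each week.
- Sessions: 12 × (2 + 1) = 36. Maximum: 36 × 2 = 72 points.
- Cuts: 50% of 72 = 36 and 75% of 72 = 54.
- The 73 possible totals become three groups: low 0-35, medium 36-53, high 54-72.
- 35/72 = 48.6% and 36/72 = 50.0% fall in different groups; 36/72 = 50.0% and 53/72 = 73.6% count as the same.

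**2. Information kept by the groups.** Assumption: percentages roughly normal with mean μ and SD σ (the article gives neither). For a shift in the mean, the fraction kept is Σ (φᵢ − φᵢ₊₁)² / Pᵢ. Here φᵢ is the normal density at each group limit and Pᵢ is the probability of the group.

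Worked case, μ = 65 and σ = 20: the limits are z = (50 − 65)/20 = −0.75 and z = (75 − 65)/20 = 0.50, with densities 0.301 and 0.352 and group probabilities 0.227, 0.465 and 0.309. The sum is 0.301²/0.227 + (0.301 − 0.352)²/0.465 + 0.352²/0.309 = 0.400 + 0.006 + 0.402 = 0.81.

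| Assumed mean | Kept, SD 10-25 |
|---|---|
| 60-70% | 63-81% |
| 75-85% | 44-76% |

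So the loss is about 20-35% at a mean of 60-70%, and about 25-55% at 75-85%.

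**3. What the full score would give.** The 95% half-width for the mean is t × SD/√n. With an assumed SD of 20 points:
- n = 10: 2.262 × 20/√10 = 14.3 points
- n = 8: 2.365 × 20/√8 = 16.7 points

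The benchmark proportion is much less precise. The smallest passing results have exact 95% intervals of 24.5-91.5% (5 of 8) and 34.8-93.3% (7 of 10). These two quantities are different, so this shows what is available and is not a like-for-like comparison.

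**4. Gender contrast.** Assumptions: mean 65%, SD 15-20 points, gender difference 20-30 points, two-sided 5%, and the same exact permutation test on the full score and on the groups coded 0/1/2. Results are simulated; each range runs over the two SDs.

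| Split | Difference | Full score | Three groups |
|---|---|---|---|
| 5 v 5 | 20 | 26-43% | 13-21% |
| 5 v 5 | 30 | 50-77% | 31-49% |
| 4 v 4 | 20 | 13-22% | 4-6% |
| 4 v 4 | 30 | 27-48% | 11-19% |

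The smallest loss is 13 − 4 = 9 points (4 v 4, 20-point difference, SD 20) and the largest is 48 − 19 = 29 points (4 v 4, 30-point difference, SD 15). A separate simulation at means of 62.5% and 75% gave losses from 12.4 − 5.4 = 7 points to 48.3 − 16.8 = 31.5 points, so the pattern does not hinge on the assumed mean of 65%.

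**The case against.** The best defence is that the groups serve the decision rule. The benchmark is the only use the article actually names for them; no sentence says that the gender analysis will use the groups. The totals are computed, the analysis plan promises descriptive statistics, and a summary of 8-10 totals would fit that promise. A condensed article may leave such a table to a fuller plan. The score also sums ordinal codes, so banding it is not unreasonable. And power is a weak yardstick for a study that is openly unpowered and whose gender analysis is labelled exploratory.

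Much of this stands, and it limits the point. A reader might infer that the raw score is thrown away; the article does not say so. A reader might also infer that most of the differences between participants are lost. The calculation does not support that: at a mean of 60-70% the groups keep 63-81% of the information. Nor is there a planned analysis relating participation to clinical change, so no loss can be claimed there. The 0-72 scale applies to people with ID. Carers on protocol B attend flexibly and have no fixed number of sessions, so it does not fit them.

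What the defence does not remove is the wording. The sentence assigns the groups to analysis in general and not to the benchmark alone. That is a stated choice, not a detail left out.

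**Conclusion.** The point holds as a minor one. As written, a primary feasibility outcome is analysed in three groups where only the benchmark calls for groups. The cost is roughly 20-35% of the information at an assumed mean of 60-70%, more at higher participation, and no mean or SD for planning the larger trial. For the exploratory gender comparison, the cost is about 9-29 points of power under the stated assumptions.

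Every one of these sizes rests on assumed means, SDs, gender differences and an even split, because the article gives none. Power on the full score stays below 50% in all the 4 v 4 settings and in 5 v 5 with a 20-point difference. It would be wrong to infer that grouping undermines the pilot's conclusions: the benchmark reads the same either way, and no conclusion depends on a gender test.

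**What to change.** Under Feasibility outcomes, change the end of the categorisation sentence so that the high, medium and low groups are used only to read the participation benchmark. Then add that participation is analysed as the percentage of the maximum score for the sessions that apply to that participant. Report individual values, mean or median, SD and a 95% CI, and make the exploratory gender comparison on that percentage by a rank or permutation test or a t-based interval.

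One detail follows from using each participant's own denominator. With a maximum of 72, no total falls between 74% and 75% (53/72 = 73.6%, 54/72 = 75.0%). With other denominators one can: 35 sessions give a maximum of 70, and 52/70 = 74.3%. Defining medium as 50% to below 75% closes that gap.

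The cost is a sentence or two of wording and one more summary to report. No new data are needed, and the benchmark and its threshold stay as they are.
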